## 6.3 Exclusion criteria

*One of the following criteria is sufficient for exclusion:*

- Absence of histological proof
- Unfavorable stage (T2c and/or PSA > 20 ng/ml and/or Gleason > 7)
- Favorable stage (T1c T2a and PSA < 10 ng/ml and Gleason < 7)
- Prior history of uncontrolled cancer and/or treated less than 5 years (except basocellular skin cancer)
- Prostate cancer previously treated with hormonotherapy
- Contraindication to MRI
- IPSS score > 10
- Recurrent or metastatic disease
- Known gold allergy
- Patient already included in another therapeutic trial of an experimental drug
- Unavailability to medical follow-up for geographical, social or psychological reasons

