### 6.6.2 Evaluation during treatment

Evaluation of tolerance according to the NCI-CTC AE v.3.0, weekly during conformal radiotherapy (first treatment phase) then before each stereotactic radiotherapy session.

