#### Non-serious adverse events

Adverse event refers to any change in the initial condition of the patient prior to treatment, including intercurrent diseases, whether the event is considered as being related to irradiation or not and occurring at any time during the study.

The nature of each adverse event is established, along with the date of occurrence, duration, severity, relationship to treatment, associated treatments and outcome. The intensity of adverse events will be graded according to the criteria defined for the disease studied (NCI-CTCAE version 3.0 criteria – appendix 10).

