### 6.8.3 Determination of the number of subjects

The number of patients required for this study was calculated using the single step Fleming method with the following hypotheses :

P0 = 85% (level of patients without any toxicity below which the method would provide no

advantage)

P1 = 95% (level of patients without toxicity expected from the proposed methods)

= 5%

= 10% , i.e. a power of 90%

To meet these conditions, the Fleming formula requires 76 evaluable patients to be included (38 by CyberKnife and 38 by linear accelerator). The study's goal will be considered achieved if, of the 76 evaluable patients, at least 70 present no grade 3-4 toxicity according to the NCI scale.

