| Also CONSIDER: Adult Respiratory Distress Syndrome (ARDS); Cough; Dyspnea (shortness of breath); Hypoxia; Infection (documented clinically or microbiologically) with Grade 3 or 4  neutrophils (ANC <1.0 x 109/L) - *Select;* Infection with normal ANC or Grade 1 or 2 neutrophils - *Select;* Infection with unknown ANC - *Select;* Pneumonitis/pulmonary infiltrates; Pulmonary fibrosis (radiographic changes). | | | | | | | | | | | | | |
| Pulmonary fibrosis (radiographic changes) | Pulmonary fibrosis | | | Minimal radiographic findings (or patchy or bi-basilar changes) with estimated radiographic proportion of total lung volume that is fibrotic of <25% | Patchy or bi-basilar changes with estimated radiographic proportion of total lung volume that is fibrotic of 25 – <50% | | Dense or widespread infiltrates /consolidation with estimated radiographic proportion of total lung volume that is fibrotic of 50 – <75% | | Estimated radiographic proportion of total lung volume that is fibrotic is ≥75%; honeycombing | | Death | | |
| REMARK: Fibrosis is usually a "late effect" seen >3 months after radiation or combined modality therapy (including surgery). It is thought to represent scar/fibrotic lung tissue. It may be dfficult to distinguish from pneumonitis that is generally seen within 3 months of radiation or combined modality therapy. ALso CONSIDER: Adult Respiratory Distress Syndrome (ARDS); Cough; Dyspnea (shortness of breath); Hypoxia; Infection (documented clinically or microbiologically) with Grade 3 or 4 neutrophils (ANC <1.0 x 109/L) – Select; Infection with normal ANC or Grade 1 or 2 neutrophils – Select; Infection with unknown ANC – Select. | | | | | | | | | | | | | |
| Pulmonary/Upper Respiratory – Other (Specify) | Pulmonary – Other (Specify) | | | Mild | Moderate | | Severe | | Life-threatening; disabling | | Death | | |
| **RENAL/GENITOURINARY** | | | | | | | | | | | | | |
| Renal failure | Renal failure | | | — | — | | Chronic dialysis not indicated | | Chronic dialysis or renal transplant indicated | | Death | | |
| ALSO CONSIDER: Glomerular filtration rate. | | | | | | | | | | | | | |
| Urinary frequency/urgency | Urinary frequency | | | Increase in frequency or nocturia up to 2 x normal; enuresis | Increase >2 x normal but <hourly | | ≥1 x/hr; urgency; catheter indicated | | — | | — | | |
| Renal/ Genitourinary – Other (Specify, ) | Renal – Other (Specify) | | | Mild | Moderate | | Severe | | Life-threatening; disabling | | Death | | |

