## Appendix 12 : The International Prostate Symptom Score (IPSS)

| **Please answer the following questions about your urinary symptoms. Write your score for each question at the end of each row.** | | | | | | | |
| --- | --- | --- | --- | --- | --- | --- | --- |
| **Over the past month, how often have you...** | **Not at all** | **Less than 1 time in 5** | **Less than half the time** | **About half the time** | **More than half the time** | **Almost always** | **Your Score** |
| **1.** ...had a sensation of not emptying your bladder completely after you finished urinating? | 0 | 1 | 2 | 3 | 4 | 5 |  |
| **2.** ...had to urinate again less than two hours after you finished urinating? | 0 | 1 | 2 | 3 | 4 | 5 |  |
| **3.** ...stopped and started again several times when you urinated? | 0 | 1 | 2 | 3 | 4 | 5 |  |
| **4.** ...found it difficult to postpone urination? | 0 | 1 | 2 | 3 | 4 | 5 |  |
| **5.** ...had a weak urinary stream? | 0 | 1 | 2 | 3 | 4 | 5 |  |
| **6.** ...had to push or strain to begin urination? | 0 | 1 | 2 | 3 | 4 | 5 |  |
|  | | | | | | | |
| **And finally..** | **None** | **Once** | **Twice** | **3 times** | **4 times** | **5 times or more** |  |
| **7.** Over the past month, how many times did you most typically get up to urinate from the time you went to bed at night until the time you got up in the morning? | 0 | 1 | 2 | 3 | 4 | 5 |  |
| **Add up your total score and write it in the box.** | | | | | | | **Total** |

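### No CTCAE urinary or rectal grade is taken at inclusion, although the primary endpoint is a CTCAE grade 3-4 count with a margin of six men and unqualified urgency is printed under grade 3

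*Protocol*

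**What the plan says.** - **Success rule (Protocol 6.8.3).** The aim is met if, of 76 evaluable men, "at least 70 present no grade 3-4 toxicity according to the NCI scale". The sentence does not mention the man's condition before treatment.
- **Definition of an adverse event (6.7.1, non-serious adverse events).** "Adverse event refers to any change in the initial condition of the patient prior to treatment". The same section asks for date of occurrence and relationship to treatment.
- **Entry limit (6.3).** The urinary symptom limit is "IPSS score > 10". It applies to the total only. Item 4 in Appendix 12, on how often the man has "found it difficult to postpone urination", scores 0 to 5 and has no cap of its own.
- **Grading scale (Appendix 10, Renal/Genitourinary).** Grade 3 urinary frequency/urgency reads "≥1 x/hr; urgency; catheter indicated". Grades 1 and 2 in that row are increases relative to normal; grades 4 and 5 are blank.
- **When grading starts (6.6.2).** "Evaluation of tolerance according to the NCI-CTC AE v.3.0, weekly during conformal radiotherapy (first treatment phase"). The inclusion examination in 6.6.1 lists no toxicity grading, and the Inclusion cell of the Adverse event row in Appendix 2 is empty. IPSS, IIEF-5 and medical history are taken at inclusion; no rectal symptom measure is scheduled there.

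**The concern.** The definition in 6.7.1 rests on a comparison with the man's state before treatment, and the endpoint is graded on CTCAE v3.0, but the two never meet: nobody records a CTCAE grade before the first fraction. For urinary urgency this matters because the grade 3 cell, as printed, is reached by urgency without a statement that it is new or worse, and the row offers no lower grade for urgency as such. A man can score 5 on IPSS item 4 and up to 5 on the other items together and still be eligible.

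Eight centres grade these men. One investigator may enter urgency at week 1 as grade 3, and another may leave it out as pre-existing. Each can defend the choice from the protocol, and there is no baseline grade to settle it. The trial has no randomised control group that would show the background level of symptoms, and the decision turns on six men. A later statistical analysis plan can define the counting rule, but it cannot supply a grade that was not collected.

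**Working it through.** **1. The plan's own figures.** Inputs from 6.8.3: a toxicity-free share of 0.85 under the null (P0) and 0.95 as hoped for (P1); alpha 5%; power 90%. Alpha is taken as one-sided, since that reproduces the stated number.

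N = [(1.645 × √(0.85 × 0.15) + 1.282 × √(0.95 × 0.05)) / 0.10]² = 75.1, rounded up to 76.

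Cut-off = 76 × 0.85 + 1.645 × √(76 × 0.85 × 0.15) = 69.7, rounded up to 70.

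With X the number of men with an event, success is X ≤ 76 − 70 = 6. Exact binomial: P(X ≤ 6 | 76, 0.15) = 0.0497 and P(X ≤ 6 | 76, 0.05) = 0.914. The design reproduces, with almost no slack on alpha.

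**2. Pre-existing symptoms counted as events.** Assume a true treatment-related rate of 5%. If k men are counted as events because of baseline symptoms, the other 76 − k may contribute at most 6 − k:

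P(success) = P(Y ≤ 6 − k), Y ~ Bin(76 − k, 0.05)

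| k | P(success) |
|---|---|
| 0 | 0.914 |
| 1 | 0.828 |
| 2 | 0.689 |
| 3 | 0.501 |

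The same effect expressed as a prevalence q, assumed independent of treatment toxicity, uses event probability 1 − 0.95 × (1 − q). P(success) is 0.612 at q = 3%, 0.380 at 5% and 0.142 at 8%. Neither k nor q can be taken from the protocol; these are assumed ranges.

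**3. Genuine events dismissed as pre-existing.** At the null rate of 15%, if d genuine events are left out, the rule passes whenever the true count is at most 6 + d:

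| d | P(X ≤ 6 + d given 76, 0.15) |
|---|---|
| 0 | 0.050 |
| 1 | 0.100 |
| 2 | 0.177 |

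So the error can run either way, depending on how each centre reads 6.7.1.

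**4. Would a simple above-baseline rule do?** Counting only grades above the man's own baseline seems natural. In the urgency row, however, grades 4 and 5 are blank, so a man at grade 3 at entry could never become an event on that term. As an upper bound, suppose such men could not become events on any term. The event probability at the null is then 0.15 × (1 − q), and the type I error becomes 0.061, 0.070 and 0.086 at q = 3%, 5% and 8%. The true figure would be lower because other urinary and rectal terms remain, but the rule needs a provision for these men.

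**The case against.** The strongest reply is that the protocol already separates old symptoms from toxicity. Under 6.7.1 an unchanged symptom is not an adverse event. The synopsis counts toxicities that occur after the start of radiotherapy, and the visits in 6.6.3 to 6.6.5 assess toxicity related to or associated with irradiation. A reader might infer that men with baseline urgency will simply be counted as grade 3 failures. The documents do not support that: read as a whole, they point the other way.

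Nor is it right that nothing is on file. The baseline IPSS records urgency, frequency and nocturia and is repeated at follow-up, so a man with a high item 4 score can be identified. Equating that score with grade 3 is an inference, since the protocol gives no mapping, and the cell places urgency beside at-least-hourly voiding and an indication for a catheter. On the rectal side, no symptom is shown that an eligible man would carry at grade 3, and the stool-count criterion for diarrhoea in Appendix 10 is already stated over baseline.

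All of this stands, and it limits the point. What remains is that the intended comparison has no baseline on the endpoint's own scale, IPSS is not a substitute for it, and a man whose mild urgency changes slightly is the hard case that neither 6.7.1 nor IPSS settles.

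**Conclusion.** A worthwhile and inexpensive improvement, not a flaw that invalidates the design. The protocol's principle is sound, but the data needed to apply it uniformly are not scheduled and cannot be recovered after treatment begins. The decision rule is sensitive: with a true 5% rate, each of the first three miscounted men costs roughly 9 to 19 points of success probability (0.914, 0.828, 0.689, 0.501), and one wrongly dismissed event at the null doubles the type I error from 0.050 to 0.100.

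These figures show what a miscount would cost, not how likely it is. They rest on assumed counts and on the assumption that the affected men are handled against 6.7.1 in one direction or the other. The baseline frequency of urgency is not in the documents. The demonstrated mechanism is urinary; the rectal grade is asked for because rectal toxicity is half of the primary objective and has no scheduled baseline measure.

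**What to change.** 1. Add CTCAE v3.0 urinary and rectal grades to the inclusion visit, before marker placement: one line in 6.6.1 and a mark in the Inclusion cell of the Adverse event row in Appendix 2.
2. In 6.8.3, refer to the definition in 6.7.1 and state that the event is grade 3-4 urinary or rectal toxicity that is new or worsened relative to the recorded baseline.
3. List separately any man at grade 3 at baseline on a urinary or rectal term. Judge worsening in these men with the help of the baseline IPSS, because the urgency row has no grade 4 or 5.
4. Report baseline grades, and a sensitivity analysis that counts every on-study grade 3-4 urinary or rectal finding in those men as an event.

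The IPSS entry limit, the sample size and the cut-off of 70 stay as they are. The cost is one CRF entry at a visit already held and a few sentences of text. Some judgement remains for the men who enter at grade 3; they should be few, and the sensitivity analysis shows whether they matter.

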## Appendix 11 : IIEF-5 questionnaire

| **In the Last 3 weeks...**  **How do you rate your confidence that you could get and keep an erection..?**  Very Low      Low      Moderate      High      Very High |
| --- |
| **When you had erections with sexual stimulation, how often were your erections hard enough for penetration..?**  Never/almost never   A few times   Sometimes (50:50)  Most times  Almost always/always |
| **During sexual intercourse, how often were you able to maintain your erection after you had penetrated (entered) your partner..?**  Never/almost never   A few times   Sometimes (50:50)  Most times  Almost always/always |
| **During sexual intercourse, how difficult was it to maintain your erection to completion of intercourse..?**  Extremely difficult    Very difficult    Difficult    Slightly difficult    Not difficult |
| **When you attempted sexual intercourse, how often was it satisfactory for you..?**  Never/almost never   A few times   Sometimes (50:50)  Most times  Almost always/always |

## Appendix 12 : The International Prostate Symptom Score (IPSS)

| **Please answer the following questions about your urinary symptoms. Write your score for each question at the end of each row.** | | | | | | | |
| --- | --- | --- | --- | --- | --- | --- | --- |
| **Over the past month, how often have you...** | **Not at all** | **Less than 1 time in 5** | **Less than half the time** | **About half the time** | **More than half the time** | **Almost always** | **Your Score** |
| **1.** ...had a sensation of not emptying your bladder completely after you finished urinating? | 0 | 1 | 2 | 3 | 4 | 5 |  |
| **2.** ...had to urinate again less than two hours after you finished urinating? | 0 | 1 | 2 | 3 | 4 | 5 |  |
| **3.** ...stopped and started again several times when you urinated? | 0 | 1 | 2 | 3 | 4 | 5 |  |
| **4.** ...found it difficult to postpone urination? | 0 | 1 | 2 | 3 | 4 | 5 |  |
| **5.** ...had a weak urinary stream? | 0 | 1 | 2 | 3 | 4 | 5 |  |
| **6.** ...had to push or strain to begin urination? | 0 | 1 | 2 | 3 | 4 | 5 |  |
|  | | | | | | | |
| **And finally..** | **None** | **Once** | **Twice** | **3 times** | **4 times** | **5 times or more** |  |
| **7.** Over the past month, how many times did you most typically get up to urinate from the time you went to bed at night until the time you got up in the morning? | 0 | 1 | 2 | 3 | 4 | 5 |  |
| **Add up your total score and write it in the box.** | | | | | | | **Total** |

**Supplementary question - Quality of life due to urinary symptoms.**

If you were to spend the rest of your life with your urinary condition the way it is now, how would you feel about that? (Please tick which best describes how you would feel.)

0. Delighted
1. Pleased
2. Mostly satisfied
3. Mixed - about equally satisfied and dissatisfied
4. Mostly dissatisfied
5. Unhappy
6. Terrible
